### 2.2 Secondary purpose

To evaluate the efficacy of escalating dose injections of RRG-003 in children with DFNB9 congenital hearing loss.

## 3. Study design

**Study type:** Interventional

**Allocation and masking:** non-randomized, open label

**Intervention model:** single arm, sequential assignment

This is a single-arm, open-label, sequential-assignment, non-randomized trial with dose ascending exploration. Considering the limited number of patients with rare diseases of Otoferlin mutations, and minimizing exposure to the risk of ineffective or low effective dose, the study design of investigational drug is as the following doses escalating protocol:

[figure not shown]

For participants who satisfy the inclusion criteria will be enrolled into this trial from with the drug concentration low dose to high dose. To begin with, equally volume mixed AAV-OTOF-N and AAV-OTOF-C drug administrate through ear canal to infuse cochlea with a micropump.

The first participant is enrolled in the dose group of 30  $\mu\text{L}$  ( $9\text{E}11$  vg/ear) with single-dose administration. If dose limiting toxicity (DLT) is not observed within 42 days after administration, the next participant can be enrolled into the dose group of 50  $\mu\text{L}$  ( $1.5\text{E}12$  vg/ear). If DLT is observed in the first participant during the 42-day DLT evaluation period, the second participant should be enrolled in the dose group of 30  $\mu\text{L}$  after the risk evaluation of the investigators. If DLT is not observed in the second participant during the 42-day DLT evaluation period, the third participant can be enrolled in 30  $\mu\text{L}$  group after the risk evaluation of the investigators. If DLTs are both observed at the first and the second participants within 42 days, the investigator can enroll one participant in the lower dose group or terminate the study after cautious evaluation. While the investigator is evaluating the safety of 50  $\mu\text{L}$ , no more than 3 cases can be extended according to the clinical risks/benefits in the group of 30  $\mu\text{L}$  dose.

The next dosage group is 50  $\mu\text{L}$  ( $1.5\text{E}12$  vg/ear). If there is no DLT observed during the 42-day DLT evaluation period after the first subject receiving a single dose, the second and the third participants can be enrolled in this dose group (the second and the third case are enrolled 14 days apart); If the number of DLT is less than or equal to 1/3 of the number of enrolled people in 50  $\mu\text{L}$  dose group, no more than 3 participants can be enrolled in this dose group (the enrollment interval is 14 days); If there is one case of DLT observed in the second or third participants during the 42-day DLT evaluation period, it is necessary to enroll 3 more participants to determine whether the 50  $\mu\text{L}$  dose is safe and tolerable. If DLT observed in the first participant during the 42-day DLT evaluation period, the second participant will be enrolled and received the injection after the risk assessment from investigators; However, if there is no DLT observed in the 42-day DLT evaluation period of the second participant, the third participant will be enrolled in this dose group after the risk assessment from investigator, and 3 more participants are required to be enrolled in the group of 50  $\mu\text{L}$  dose (interval 14 days) for DLT evaluation. If 3-5 participants are evaluated without DLT events or 6 participants evaluated with  $\leq 1$  DLT event in this dosage group, investigators can carry out extended trials following comprehensive evaluation. During the period of expanding study, the investigator may enroll more participants in 30  $\mu\text{L}$  or 50  $\mu\text{L}$  dosage group for single injection or

double injection (including bilateral ear administration or repeated administration in single ear), or explore the administration of 70 µL does. If the number of participants is not less than 3 and no DLT is observed within 42 days, the investigator can explore double injection of administration in the 70 µL dose group. Once the number of participants with DLT in this dose group is more than 1, the exploration of this dose group should be stopped; the investigator could return to previous dose group after the full evaluation.

The results of first participant in each dose group should be promptly reported to the ethics committee. During dose escalation among groups, investigators can perform expanding study in next dose group or previous dose group, based on the assessment of clinical risk and benefit. Investigators should apply in advance to adjust the number of participants strictly based on the study results. In appropriate circumstances, investigators may terminate the clinical trial in either dose group.

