## **5. The number of cases required to achieve the intended purpose of the study based on statistical principles**

According to the description above, the total number of effective cases was 4-12. Two to three dose groups were set for administration, and the exploration dose was set as 30  $\mu$ L (9.0E11 vg/ear), 50  $\mu$ L (1.5E12 vg/ear), 70  $\mu$ L (2.1E12 vg/ear). The exploration age was 1-18 years old. An effective case was defined as a subject who was given drug in compliance with the protocol and was observed for 6 weeks at least. The actual number of subjects can be adjusted according to trial requirements.

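### The final protocol's dose rules give no single action at 50 µL once a second DLT occurs

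*Supplement*

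**What the plan says.** All references are to the final protocol (v5). DLT at week 6 is the primary indicator (section 11), and the DLT window is 42 days (section 3.1). For 50 µL, section 3 sets out these rules in one paragraph:

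- **First cohort.** If participant 1 has no DLT over 42 days, "the second and the third participants can be enrolled in this dose group", 14 days apart.
- **One-third rule.** "If the number of DLT is less than or equal to 1/3 of the number of enrolled people" in the 50 µL group, then "no more than 3 participants can be enrolled in this dose group (the enrollment interval is 14 days"). The denominator is children enrolled. The text does not say whether three is a total or an addition, or whether the rule may be used again.
- **One DLT in participant 2 or 3.** "it is necessary to enroll 3 more participants to determine whether the 50" µL dose is safe and tolerable.
- **DLT in participant 1.** Participant 2 is treated after a risk assessment. If participant 2 has no DLT, participant 3 follows, and three more are then required. No condition is placed on participant 3's outcome.
- **Extension.** "If 3-5 participants are evaluated without DLT events or 6 participants evaluated with" at most one DLT, extended trials may be opened. The denominator is children evaluated.
- **Stop.** "Once the number of participants with DLT in this dose group is more than 1, the exploration of this dose group should be stopped". The sentence immediately before it concerns double injection at 70 µL.

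For 30 µL, if both of the first two participants have a DLT, "the investigator can enroll one participant in the lower dose group or terminate the study after cautious evaluation". Sections 5 and 6.1 define no dose below 30 µL. Section 5 states that "the total number of effective cases was 4-12" and that the number can be adjusted.

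**The concern.** These sentences turn the primary safety endpoint into decisions to dose more children, to give second injections or to go to 70 µL. They use three different bases: a fraction of those enrolled, a count among those evaluated, and a bare count in a group that is not named. If two competent readers can take the same DLT record at 50 µL and reach different actions, the decision rests on the reading and not on the plan. That matters most after a second DLT, when a clear rule is most needed.

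**Working it through.** **The plan's own number.** Section 5 says the range 4-12 follows from the design but gives no formula. The lower end can be counted: 1 at 30 µL + 3 at 50 µL = 4. The upper end has no unique count: 3 + 6 + 3 = 12 is one reading, and (1 + 3) + 6 + 3 = 13 and (3 + 3) + 6 + 3 = 15 are others.

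**The 50 µL rules side by side.**

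| DLT record at 50 µL | One-third rule | Extension criterion | Stop, if it covers 50 µL | Other explicit instruction |
|---|---|---|---|---|
| 1 of 3 | met | not met | not triggered | three more required |
| 2 of 2 | not met | not met | stop | none |
| 2 of 3 (participants 1 and 3) | not met (2/3 > 1/3) | not met | stop | three more required |
| 2 of 3 (participants 2 and 3) | not met | not met | stop | none |
| 1 of 6 | met | met | not triggered | extension may open |
| 2 of 6 | met, if reusable (2/6 = 1/3) | not met | stop | none |

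Through 1 of 3 and 1 of 6 the rules form an ordinary 3+3 pattern. The difficulty begins with the second DLT:

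- At 2 of 6, the one-third rule (if it may be reapplied) and the stop (if it covers 50 µL) point in opposite directions. If the stop covers only 70 µL, no numerical stop exists at 50 µL.
- At 2 of 3, the instruction depends on which children had the DLTs. This does not require reusing the one-third rule.

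**Denominator.** The 14-day interval is shorter than the 42-day window. As an illustration, take the earliest permitted dates and treat enrolment and dosing as the same day. Participant 1 is dosed on day 0 and cleared on day 42, participant 2 is dosed on day 42 and participant 3 on day 56. A fourth child could be enrolled on day 56 + 14 = 70. The windows of participants 2 and 3 close only on days 42 + 42 = 84 and 56 + 42 = 98. On day 70 the fraction would rest on three enrolled children, of whom one has been fully evaluated.

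**How often these states arise.** The plan states no DLT rate, so p is assumed, with children independent.

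- Two or more DLTs in the first three: 3p²(1−p) + p³. At p = 0.30: 3(0.09)(0.70) + 0.027 = 0.216. By pattern, DLTs in participants 1 and 2 contribute 0.090, in 1 and 3 only 0.063, and in 2 and 3 only 0.063.
- 1 of 3, then 1 of 3: [3p(1−p)²]². At p = 0.30: 0.441² = 0.194.

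| Assumed p | ≥2 in first 3 | 1/3 then 1/3 | Sum |
|---|---|---|---|
| 0.10 | 0.028 | 0.059 | 0.087 |
| 0.20 | 0.104 | 0.147 | 0.251 |
| 0.30 | 0.216 | 0.194 | 0.410 |
| 0.40 | 0.352 | 0.187 | 0.539 |
| 0.50 | 0.500 | 0.141 | 0.641 |

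**The case against.** Several counterarguments have force.

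- **Different decisions.** Enrolling up to three more children and opening an extension are separate steps, so the one-third rule and the extension criterion do not conflict by themselves. A reader might infer that the rules contradict each other throughout. They do not: opposite orders at 2 of 6 need two readings that the text does not force, namely that the one-third rule is reusable and that the stop covers 50 µL. The nearest antecedent of the stop is in fact 70 µL. On that natural reading the fault is a missing 50 µL stop rule.
- **A cap of three and a requirement of three are compatible.** Together they give exactly three.
- **General discretion exists.** At 2 of 2 neither the continuation nor the extension permission is met. Section 3 also lets investigators terminate in either dose group, and section 10 gives general suspension grounds. This stands, but discretion is not a stated action.
- **Some branches may be closed.** The Protocol Amendments section cites no DLT at 30 µL and 50 µL. If so, the branches that start with a DLT in a first participant, including the undefined lower dose at 30 µL, may be residue. The log gives no counts. A later second DLT at 50 µL remains possible. Given no DLT in participant 1 and p = 0.30, the chance of DLTs in both 2 and 3 is 0.09, and of one DLT there followed by 1 of 3 is 0.42 × 0.441 = 0.185.
- **The escalation figure is not shown** in the text reviewed and might settle the intent. The wording would still have to agree with it.

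**Conclusion.** The point holds as an indeterminacy. After a second DLT at 50 µL, section 3 does not yield one action. Either an unnamed stop rule meets an enrolment permission, or there is no numerical stop. One 2-of-3 pattern carries an instruction to enrol three more, while the other 2-of-3 pattern and 2 of 2 have no explicit action. At an assumed DLT rate of 30%, the two groups of states have probabilities 0.216 and 0.194; the sum runs from 0.087 at 10% to 0.641 at 50%.

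Two stronger inferences are not supported:

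- A reader might compare at most 2 of 6 with at most 1 of 6 as fixed binomials (0.680 against 0.351 at a rate of 1/3) and conclude that the rules differ two- to three-fold. Enrolment is staged, however. If 0 of 3 passes and 1 of 3 fills to six, the figures are 0.626 against 0.428 at 1/3, and 0.313 against 0.172 at 1/2. Even these treat two separate decisions as one.
- A reader might also infer that the path must exceed 12 children. The count of 13 takes optional elements at their maximum, 12 is equally available, and section 5 allows adjustment.

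Nor does the plan claim an error rate for its dose rule: section 15.2 is mainly descriptive.

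**What to change.** Reconcile the section 3 passages and the escalation figure into one table per dose group, mapping the number DLT-evaluable and the number with DLT to a single action. The table should:

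- cover every state with two or more DLTs at 50 µL, including 2 of 2, both 2-of-3 patterns and 2 of 6;
- use one denominator and say how children still inside the 42-day window are counted;
- say whether the one-third rule may be reapplied;
- name the group that the stop sentence governs;
- define or remove the lower dose group at 30 µL.

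The thresholds and actions are for the sponsor and investigators to set. Then check that the range of 4-12 agrees with the table. The cost is a wording amendment with ethics review. No new data or procedures are needed, and the stated range may need restating.

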### 3.1 Dose limiting toxicity (DLT)

Dose limiting toxicity (DLT) is evaluated within 42 days after administration of RRG-003 according to Common Terminology Criteria for Adverse Events, NCI-CTCAE V5.0. DLT is defined as hematologic toxicity  $\geq$  grade 4, nonhematologic toxicity  $\geq$  grade 3, or aural toxicity in grade 2 or 3 within 6 weeks. Aural toxicity was listed as follow:

| Adverse Events               | Grade 2 ear adverse events                                                                                  | Grade 3 ear adverse events                                                                              |
|------------------------------|-------------------------------------------------------------------------------------------------------------|---------------------------------------------------------------------------------------------------------|
| Ear pain                     | Moderate pain; limiting instrumental Activities of Daily Living (ADL)                                       | Severe pain; limiting self care ADL                                                                     |
| External ear pain            | Moderate pain; limiting instrumental ADL                                                                    | Severe pain; limiting self care ADL                                                                     |
| Hearing impaired (Pediatric) | Pediatric (on a 1, 2, 3, 4, 6, and 8 kHz audiogram):
Threshold shift >20 dB at 4 kHz in at least one ear | Pediatric (on a 1, 2, 3, 4, 6, and 8 kHz audiogram):
Hearing loss sufficient to indicate therapeutic |

|                                                |                                                                                                                                 |                                                                                                                                                                                                         |
|------------------------------------------------|---------------------------------------------------------------------------------------------------------------------------------|---------------------------------------------------------------------------------------------------------------------------------------------------------------------------------------------------------|

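### The 50 µL continuation fraction counts children enrolled, the expansion rule counts children evaluated, and nothing says how a child still inside the 42-day DLT window counts

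*Supplement*

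**What the plan says.** All references are to the final protocol (version 5.0).

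- **Continuation fraction (Section 3, 50 µL group).** "If the number of DLT is less than or equal to 1/3 of the number of enrolled people" in the 50 µL group, then "no more than 3 participants can be enrolled in this dose group (the enrollment interval is 14 days"). I read this as allowing children 4 to 6.
- **Spacing of children 2 and 3.** Child 1 must pass 42 days without a DLT. After that, "the second and the third case are enrolled 14 days apart".
- **DLT window (Section 3.1).** "Dose limiting toxicity (DLT) is evaluated within 42 days after administration of RRG-003".
- **Clause for one DLT in child 2 or 3 (Section 3).** Three further children are called for, to settle whether the dose is tolerable.
- **Expansion rule (Section 3).** "If 3-5 participants are evaluated without DLT events or 6 participants evaluated with" at most one DLT event, the investigators may extend the trial. The count here is of children evaluated.
- **Stop rule (Section 3).** "Once the number of participants with DLT in this dose group is more than 1", exploration of that group stops. This follows the sentence on 70 µL and probably concerns that group.

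Section 11 makes DLT at week 6 the primary indicator. Section 15 defines neither a DLT rate nor a DLT-evaluable set.

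**The concern.** A child's DLT status is known only after 42 days, or earlier if a DLT occurs. A child dosed two weeks ago still adds one to an enrolled denominator and so counts as a full DLT-free child. No clause requires children 2 and 3 to finish the window before the fraction is applied. Followed as written, the plan can permit a further child while DLTs that have not yet appeared would take the group over its own limit of one third.

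The numerator is also unsettled. The 50 µL rules speak of DLTs and DLT events, and the stop rule of participants. The Section 3.1 table has overlapping rows, such as vertigo and vestibular disorder, or middle ear inflammation and otitis media. With three children enrolled, one child registering in two rows would turn 1/3 (pass) into 2/3 (fail). This error runs in the opposite direction.

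At stake is the dosing of further children with a treatment that cannot be withdrawn once given.

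**Working it through.** The protocol states no operating characteristic for these rules, so there is no figure of its own to reproduce.

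**Inputs.** From Section 3: the limit of 1/3, 42 days clear for child 1, and the 14-day intervals. From Section 3.1: the 42-day window. Assumptions: child 4 follows child 3 after 14 days, the fraction is checked at each enrolment, child 1 has no DLT, and DLT onset is uniform over 42 days.

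**Step 1: follow-up behind the denominator.** The earliest dosing days for children 1 to 6 are 0, 42, 56, 70, 84 and 98. Observed days = sum of min(42, days since dosing). Implied days = 42 × number enrolled.

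| Before child | Observed days | Implied days | Observed share | Shortfall | Windows still open |
|---|---|---|---|---|---|
| 4 (day 70) | 42+28+14 = 84 | 126 | 67% | 33% | 2 of 3 |
| 5 (day 84) | 42+42+28+14 = 126 | 168 | 75% | 25% | 2 of 4 |
| 6 (day 98) | 3×42+28+14 = 168 | 210 | 80% | 20% | 2 of 5 |

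If child 4 waits until child 3's window closes (days 98, 112 and 126 for children 4 to 6), the shortfalls are 0% (126/126), 16.7% (140/168) and 20% (168/210).

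**Step 2: where the denominators give different answers.** Take evaluated to mean window complete or DLT already seen.

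- Before child 4, no DLT seen: 0/3 against 0/1. Both permit.
- Before child 4, one DLT seen (child 2 or 3): 1/3 permits, 1/2 does not.
- Before child 4, two seen: 2/3 on both. Neither permits.
- Before child 5: they differ only if the single DLT is in child 2 (1/4 against 1/2).
- Before child 6: they never differ.

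**Step 3: children 2 and 3 would both have a DLT (2/3, above the limit).** At day 70, child 2's DLT has appeared with probability 28/42 = 2/3 and child 3's with probability 14/42 = 1/3.

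- Both seen: 2/3 × 1/3 = 2/9.
- Exactly one seen: 2/3 × 2/3 + 1/3 × 1/3 = 5/9.
- None seen: 1/3 × 2/3 = 2/9.

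The enrolled fraction permits child 4 unless both are seen: 7/9 = 78%. The evaluated fraction permits only if none is seen: 2/9 = 22%. These are conditional on both children going on to a DLT. At an assumed DLT risk of 0.33, the joint probabilities over all courses with child 1 clear are 0.33² × 7/9 = 8.5% and 0.33² × 2/9 = 2.4%. At a risk of 0.5 they are 19% and 6%.

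**The case against.** The strongest reply is that the neighbouring clause already covers the disputed state. Every disagreement in Step 2 has exactly one DLT seen, in child 2 or 3, and there three more children are called for on either denominator. At a risk of 0.33, child 4 may be dosed with probability 1 − 0.33² × 2/9 = 97.6% on the enrolled fraction. On the evaluated one it is (1 − 0.33 × 2/3)(1 − 0.33 × 1/3) = 69.4%. A reader might infer that this gap is the number of extra dosings. It is not, because the whole gap lies in that state. What survives is that the clause speaks of one DLT and does not say whether the other child's window must have closed. That child may become the second case.

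It is also fair to say that simply writing evaluated for enrolled is no cure. It would set the fraction (1/2, no enrolment) against the neighbouring clause (enrol three more), and it would change nothing when no DLT has yet been seen.

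Other stronger readings fail too:

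- **That pending children are unobserved.** Section 20 has them in hospital on days 1 to 7 and seen at weeks 2 and 4.
- **That the rate is diluted at every dosing.** Child 2 follows a full window, child 3 is not governed by the fraction, and with no DLT the fraction is zero on either denominator. The text gives no wait before child 4 and no re-check before children 5 and 6. The escalation diagram is not visible in the copy reviewed.
- **That the primary DLT result is biased.** Section 11 fixes it at week 6, and Section 5 requires at least six weeks of observation for an effective case. Nothing carries the interim fraction into the final rate.
- **That events are certainly counted instead of children.** A number of DLTs set against a number of people reads most naturally as children. The wording merely leaves the other reading open.

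**Conclusion.** The point holds as an inconsistency and an omission in Section 3. Two rules for the same dose group use different denominators, and the plan does not say how a child inside the 42-day window counts or when the fraction is checked.

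On the fastest schedule, follow-up falls short of what the denominator implies by 33%, 25% and 20% before children 4, 5 and 6. It falls short by 0%, 16.7% and 20% if child 4 waits for child 3's window. If children 2 and 3 would both have a DLT, child 4 is permitted in 78% of cases on the enrolled fraction and 22% on an evaluated one. These two figures rest on the fastest schedule, uniform onset and child 1 being clear, but not on the assumed DLT risk. They describe the fraction alone, without the neighbouring clause.

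The practical consequence is that a further child can be dosed before pending DLTs are known. The matter should be corrected because the rule governs dosing of children and the correction is cheap.

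**What to change.** The sponsor should reconcile the Section 3 clauses so that:

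- the continuation fraction, the clause for one DLT in child 2 or 3 and the expansion rule use one stated denominator;
- the numerator is children with at least one DLT, not events;
- the time at which the fraction is checked is stated, including whether it is re-applied before children 5 and 6;
- the counting of children still inside the 42-day window is stated, including when no DLT has yet been seen and when one has been seen with another child pending.

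Section 15 should define the final DLT rate as children with a DLT divided by children who completed the 42-day window or had a DLT.

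The thresholds, the enrolment interval and the choice of dosing rule are for the sponsor, and none is proposed here. The change needs a short amendment and no extra children or visits. Its downside is that an enrolment decision may sometimes have to wait for a window to close.
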